## Abstract

**Background:**

Testicular cancer diagnosis and treatment, especially given its threat to sexuality and reproductive health, can be distressing in the formative period of young adulthood and the majority of young survivors experience impairing, distressing, and modifiable adverse outcomes that can persist long after medical treatment. These include psychological distress, impairment in pursuit of life goals, persistent physical side effects, elevated risk of secondary malignancies and chronic illness, and biobehavioral burden (e.g., enhanced inflammation, dysregulated diurnal stress hormones). However, few targeted interventions exist to assist young survivors in renegotiating life goals and regulating cancer-related emotions, and none focus on reducing the burden of morbidity via biobehavioral mechanisms. This paper describes the methodology of a randomized controlled biobehavioral trial designed to investigate the feasibility and preliminary impact of a novel intervention, Goal-focused Emotion-Regulation Therapy (GET), aimed at improving distress symptoms, emotion regulation, goal navigation skills, and stress-sensitive biomarkers in young adult testicular cancer patients.

**Methods:**

Participants will be randomized to receive six sessions of GET or Individual Supportive Therapy (ISP) delivered over 8 weeks. In addition to indicators of intervention feasibility, we will measure primary (depressive and anxiety symptoms) and secondary (emotion regulation and goal navigation skills, career confusion) psychological outcomes prior to (T_0_), immediately after (T_1_), and 12 weeks after (T_2_) intervention. Additionally, identified biomarkers will be measured at baseline and at T_2_.

**Discussion:**

GET may have the potential to improve self-regulation across biobehavioral domains, improve overall cancer adjustment, and address the need for targeted supportive care interventions for young adult cancer survivors.

**Trial registration:**

Clinicaltrials.gov, NCT04150848. Registered on 28 October 2019.

## Background

The development of effective interventions that prevent, control, and eliminate physical, psychological, and behavioral adverse effects of cancer in young adult survivors is a public health priority [1]. Testicular cancer is the most prevalent non-skin cancer among men in late adolescence and early adulthood, and rates of new diagnoses have been rising over the last decade [2]. Ensuring robust health-related quality of life is essential in this group, as they face both psychological and physical impact from potential loss of a reproductive organ and long-term functional impacts of chemotherapy, radiation therapy, and/or surgery [3–5]. Further, long-term sequelae are more severe and persistent in those receiving chemotherapy, and include peripheral neuropathy, hearing loss, hypogonadism, infertility, secondary malignancies, long-term hearing loss, sexual dysfunction, and development of cardiovascular disease [4, 6–10].

Psychosocial impact is also substantial as the prevalence of depressive symptoms and anxiety in testicular cancer exceeds that in the general population [3]. Common concerns include body image disruption, social relationships, fertility and sexual distress, masculinity threat, work-related problems, and worry about the future [5, 11–13] and nearly two-thirds of testicular cancer survivors report unmet survivorship needs [13–15], most commonly relating to supportive care, survivorship information, managing distress, fertility, relationships and self-image, and occupational problems [14–17]. Yet there is a paucity of psychosocial supportive cancer interventions for young adults. In a systematic review, Walker et al. [18] identified only 18 psychosocial interventions for young adult survivors, and only 8 of these were tested in a randomized controlled trial. Also, none of these interventions were tailored to the needs of young men, and none targeted developmentally informed processes of self-regulation.

Adjustment to challenged goals constitutes adaptive self-regulation [19] and may be particularly critical when cancer occurs in early adulthood [20, 21]. Cancer diagnosis and treatment present circumstances that challenge the achievement and pursuit of meaningful life and developmentally timed goals (e.g., pursuit and maintenance of dating and sexual relationships, identification of values-driven occupational pursuits, achievement of independence from parents) [22, 23]. Cancer-related goal disturbances are associated with chemotherapy receipt and a host of behavioral and psychological symptoms, including depression, fatigue, pain, and cognitive complaints [24]. Concerns about the achievement of life goals are especially distressing for adolescents and young adult survivors [25–27], who are negotiating greater autonomy across life domains and are oriented toward achievement of future goals. Goal navigation skills include the ability to identify new and existing goals; together with emotion-regulating coping behaviors, they have the potential to support cancer-related well-being [28–31], and they might play a role in regulation of stress-sensitive biobehavioral factors, including inflammatory and neuroendocrine processes [32, 33].

This manuscript describes the methodology of a randomized controlled biobehavioral pilot trial designed to investigate the feasibility of Goal-focused Emotion-Regulation Therapy (GET), a novel intervention aimed at improving distress symptoms, self-regulation (i.e., emotion regulation and goal navigation skills), and stress-sensitive biomarkers in young adult testicular cancer patients with the overarching goal of establishing whether a future larger-scale trial can and should be conducted in this manner. The intervention will be administered in six sessions delivered over 8 weeks to a sample of 60 young adult (ages 18–39 years) recent testicular cancer survivors. As an external pilot study, a major focus will be on testing data collection procedures and measurement strategies, optimizing the recruitment plan, testing randomization, and informing appropriate sample size estimates. Examination of the integrity and acceptability of the study protocol will be of primary focus.

### Hypotheses

We hypothesize that young adult testicular cancer survivors will confirm the formative findings that the GET intervention is feasible, tolerable, and acceptable. Furthermore, we expect that, in comparison to those in Individual Supportive Therapy (ISP), participants receiving GET will have a measurable, positive improvement on potential primary and secondary outcomes. Primary outcomes of consideration are change in psychological distress (i.e., depressive and anxiety symptoms) from baseline to 12 weeks post intervention and change in systemic inflammation markers (i.e., IL-6, IL-1ra, CRP, sTNFαRII) and salivary cortisol regulation (i.e., diurnal cortisol slope and daily cortisol output) from baseline to post intervention. However, results related to changes in distress symptoms will inform sample size estimates in future trials. Of additional focus are changes in self-regulatory processes (i.e., emotion regulation and goal navigation skills, career confusion) from baseline to 12 weeks post intervention.

## Methods

### Study design

Study goals and design were informed in part by the SPIRIT guidelines [34], previous cancer control intervention research [35, 36], and models of translational research for behavioral interventions [37]. This study will utilize a randomized, controlled, repeated-measures design to investigate the feasibility of studying GET relative to a well-matched comparator (i.e., ISP) to improve identified variables in young adult testicular cancer patients. See Fig. 1.

**Fig. 1 Fig1:**
[figure not shown]
Study schematic. GET Goal-Focused Emotion-Regulation Therapy, ISP Individual Supportive Psychotherapy, R randomization, Sn session number, T_0_ baseline, T_1_ post Intervention, T_2_ 12-week follow-up

The replication and extension of the promising and preliminary results of our formative research (described in the following) will contribute to satisfying the critical need for accessible, feasible, effective, and scalable interventions for young adult survivors with the goal of ameliorating long-term negative effects of cancer and cancer treatment. Participants will be 60 young adults with testicular cancer who have completed treatment (including chemotherapy) and will be randomized 1:1 into GET or ISP using a block of 10 randomization design. A central randomization scheme will be used in which a research recruiter will contact a central methods center by secure computer for allocation assignment for newly enrolled participants to maintain concealment of the randomization sequence. The sequence will be generated by a computer randomization program.

Sample size was determined by balancing realistic recruitment estimates and minimal sample requirements for planned analyses. Informed consent will be obtained individually following eligibility screening and prior to data collection. The interventions will be delivered face to face in a clinical setting. However, to enhance accessibility, telephone sessions will also be possible for those with accessibility barriers.

Participants will complete questionnaire assessments at baseline (T_0_), at the completion of the last GET or ISP session (T_1_), and at 12 weeks following completion of the last GET or ISP session (T_2_). In addition, biological specimens will be collected at T_0_ and at T_1_. These include the collection of plasma via venipuncture (in the clinic) and samples of saliva (at home). Saliva is collected over 2 days at each assessment point upon awakening, 30 min later, 8 h later, and at bedtime [38]. Questionnaire data will be collected via an online password-protected data collection platform. All participants will be offered $50 at each data collection point for completion of assessments and collection of biomarkers (and $25 without biomarker assessment).

All study procedures will be reviewed and approved by the University of California, Irvine and Memorial Sloan Kettering Cancer Center Institutional Review Boards.

Given the assessed low risk of trial participation, serious adverse events and harms are not anticipated; no formal stopping rules are designated. Likewise, a study-specific data monitoring committee was not considered. However, the institutional data safety board for cancer studies is available for consultation and the investigational team will meet weekly to monitor study progress and activities.

### Participants

Participants will be young adults with a diagnosis of testicular cancer who have completed active treatment (surgery + chemotherapy) and present with elevated distress and/or deficits in goal navigation skills. We will enroll participants from the Chao Family Comprehensive Cancer at the University of California, Irvine and Memorial Sloan Kettering Cancer Center, and various young adult community-based support groups or children’s hospital settings.

### Eligibility

Participants will be initially identified through electronic medical record screening or identified by clinic personnel, or will self-identify in response to study announcements.

Determination for study eligibility will occur via screening by a research study assistant. Participants eligible for this study will be those who: are between the ages of 18 and 39 years at the time of consent; have a confirmed diagnosis of testis cancer (any stage); have completed chemotherapy for testis cancer within 2 years prior to consent; have fluency in English (per self-report); and exhibit suboptimal self-regulation, evidenced by a score of 1.8 or below on the goal navigation scale [28] or a score of 4 or greater on the Distress Thermometer (DT) [39].

Exclusion criteria include: lifetime history of bipolar disorder, schizophrenia, or schizoaffective disorder (per self-report); an active suicide plan; presence of a disorder that compromises comprehension of assessments or informed consent information (e.g., dementia); and self-reported medical condition or medication use known to confound measures of systemic inflammation (e.g., autoimmune disorder, active infection; myocardial infarction or stroke in the last 6 months; recent vaccination for viral disease); and daily smoking [38, 40].

Participation will not require alteration to usual care including use of any medication or psychotherapy.

### Intervention conditions and delivery

#### Goal-Focused Emotion-Regulation Therapy

##### Development of GET intervention

The identification of core components and the development of the GET intervention come from preliminary empirical work with young adult testicular cancer survivors. First, an in-depth interview study of a diverse sample (*N* = 21; 48% ethnic minority) of young adult survivors of testicular cancer [41] revealed that young men perceive that life goals are an important aspect of adapting to testicular cancer, and identified goal and values clarification, engagement and disengagement from life goals, and the ability to express and process emotional responses to disrupted goals among critical self-regulation skills regarding behavioral and emotional responses to cancer-related stressors. Second, they identified a preference for action orientation, positivity, achievement, and practical realism. This included an inclination toward the use of an active, approach-oriented stance to pursuing prior goals and/or reengaging with new goals after cancer. Third, findings suggested that when goal navigation capacity was low or impaired, young men were less likely to benefit from their efforts at approach-oriented coping.

In a follow-up observational study of the same population (*N* = 171), Hoyt et al. [28] identified measurable goal-related processes including “goal navigation”, or the capacity to identify and pursue valued life goals. Goal navigation demonstrated cross-sectional associations with aspects of cancer-related adjustment. In regression analyses controlling for age and time since diagnosis, goal navigation was positively associated with emotional (*B* = 0.35, *p* < 0.001), social (*B* = 0.24, *p* < 0.01), and functional (*B* = 0.28, *p* < 0.001) well-being [41]. Further, a theoretical model of goal navigation using a self-regulation framework was identified and tested [42]. Goal navigation skills were negatively correlated with depressive symptoms (*r* = − 0.41, *p* < 0.01) and positively correlated with physical functioning (*r* = 0.28, *p* < 0.01), and these were mediated by possessing a sense of meaning in goal pursuit (indirect effects: depressive symptoms (*r* = − 0.50, *p* < 0.05), physical health (*r* = 0.34, *p* < 0.05)) and emotion regulation skill (indirect effects: depressive symptoms (*r* = − 0.08, *p* < 0.05), physical health (*r* = 0.11, *p* < 0.05)).

In a follow-up, at-home monitoring study (unpublished data) to examine associations of goal navigation skill, emotion regulation, and salivary markers of diurnal cortisol and α-amylase, the use of emotion regulation skills and salivary measures were collected daily for 2 days. Low levels of goal navigation capacity were significantly associated with greater use of less constructive emotion regulation strategies and higher daily salivary cortisol output (area under the curve). Poor self-regulation skills underscore dysregulation of biological processes with strong potential to lead to declines in physical health and mood.

Taken together, these findings underscored development of GET and an initial intervention manual which was tested to establish the feasibility and acceptability for the patient population. This included initial patient focus group interviews, as well as a series of individual patient interviews to gain feedback into session content, intervention length and format, and structured at-home components. A revised manual emerged that, based on findings, included more “normalization of experience”, opportunities to address cancer-specific topics (e.g., cancer-related disclosure, self-care after cancer), and bolstering of emotion regulation skill-building.

Next, the revised intervention was pilot tested with six young adult testicular cancer patients to assess tolerability, acceptability, adherence, and retention. This was done through examination of treatment completion and engagement with at-home exercises as well as in-depth post-participation interviews. Supporting tolerability and acceptability, all six participants completed all study sessions with no adverse events. Also, participants’ engagement with assigned at-home exercises were coded as “attempted/not attempted” to inform adherence. Moderate adherence was observed with 78% of assigned activities attempted. Interview transcripts were analyzed with a targeted inductive procedure of thematic analysis. This involved thorough reading and review of transcripts, synthesis of key conceptual findings, and the generation of descriptive conclusions. Conclusions identified eagerness for a survivorship intervention, affirmation of the importance of the identified intervention targets, satisfaction with the intervention length and depth, and desire for study interventionists to challenge participants to “go deeper” in the process of identifying and processing emotions. Participants also identified the desire to hear more perspectives from other testicular cancer survivors. Finally, the manual was further refined based on interview findings. This included the inclusion of patient quotes in study participant hand-outs.

##### GET intervention components

GET is a six-session intervention delivered over 8 weeks to enhance self-regulation through improved goal navigation skills, improved sense of meaning and purpose, and better ability to regulate specific emotional responses. GET draws heavily from the principles of Hope Therapy [43], with an emphasis on goal navigation skill-building. Components of Hope Therapy have been used successfully in cancer survivorship interventions [44]. This includes work on goal-setting with a focus on assessing progress toward achieving specific, realistic, and measurable goals. Patients identify value-derived goals (i.e., goals for the most important domains of one’s life) and ones sufficiently important to sustain movement toward them in the short-term future. They discuss their goal possibilities, providing a forum to ensure that goals are manageable and consistent with identified values. Patients learn strategies to refine their goals (e.g., approaching goals rather than avoiding obstacles, defining markers of progress), generate pathways to goals, and address potential obstacles and blockages. Additionally, goals provided the context for demonstrations of agentic thinking (e.g., I will be able to do this) and interventions to increase agentic thinking. Specific attention is given to career/education-related goals. Emotion regulation components include basic cognitive restructuring skills, cognitive distancing, and coping efficacy skills (matching the correct coping skill to specific circumstances) (see Table 1).

**Table 1 Tab1:** GET session guide

Session	Session focus
1	Review of cancer-related experiences and influences on goal pursuits; psychoeducation regarding emotions, skills, and values
2	Values clarifications and emotional awareness
3	Achievability of goals, cognitive skills training
4	Goal pathway mapping, navigating blocked goals and re-directing energy
5	Goal motivation and agentic actions, self-care behavior
6	Goal pursuits moving forward

*GET* Goal-Focused Emotion-Regulation Therapy

#### Individual Supportive Psychotherapy

ISP will be utilized as the comparison treatment condition in this study. ISP is one of the predominant approaches to community-based supportive care in psychosocial oncology. In this study, ISP is adapted from the Supportive Group Psychotherapy manualized intervention [45], and subsequently adapted further for use in our pilot work for young adult testicular cancer patients. This intervention includes six sessions of Individual Supportive Psychotherapy utilizing an approach based on models described by Rogers [46, 47] and Block [48], including components of genuineness, unconditional positive regard, and empathic understanding through reassurance, explanation, guidance, suggestion, encouragement, affecting changes in patient’s environment, and permission for catharsis [48]. ISP also emphasizes maintaining focus on the cancer experience, supporting participants in the “here and now”, fostering expression of emotion and discussion of difficult topics, and creating a sense of being understood [45]. The manual offers instructions on how to avoid therapeutic techniques associated with other treatment modalities (e.g., CBT, interpersonal psychotherapy).

### Intervention delivery

GET and ISP will be delivered by at least a master’s-level mental health clinician interventionist who will receive intensive training prior to delivering the intervention and regular supervision after each session. All interventionists will be male. Therapists without prior GET experience will conduct one or two training cases with patients not enrolled in the proposed study. Participants consented as training cases will not be randomized and will not complete any formal assessments.

Sessions will be audio recorded so that treatment fidelity can be regularly monitored and independently rated by trained research assistants.

Participants will be permitted to continue to see any outside mental health professionals during the trial. In these instances, outside interventions will be documented and controlled for during data analysis.

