##### Demographic and clinical information

Demographic information, past/current psychosocial service use, support needs, intervention preferences, and perceived barriers are assessed through Likert-scale ratings and open-ended items. Clinical information will also be assessed via medical record review and via self-report. In addition, we will thoroughly assess for medical comorbidities and physical health symptoms.

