#### Data analysis

Standard descriptive statistics will be used to report baseline participant characteristics by condition. For continuous variables with markedly non-normal or skewed distributions, appropriate transformations may be required, such as natural logarithms, and will be applied as necessary and appropriate. We will perform analysis according to the intention-to-treat principle (i.e., participants will be analyzed according to the treatment group to which they will be randomly allocated regardless of dropout or treatment adherence status).

Change from baseline will be calculated across variables. Follow-up scores on the identified variables will be compared between study conditions (adjusting for baseline), via repeated-measures analysis of covariance (ANCOVA). We will also reference established cutoff values for clinically meaningful differences for scores on the HADS to identify ranges and patterns of change. Mixed-effects models will be used to model the scores over time for each group. Time since diagnosis, education, marital status, medical comorbidities, and age will be examined as potential covariates to model.

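### Adjusting for outside mental health care used during the trial, rather than at entry, could move the GET–ISP distress contrast away from the intention-to-treat effect

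*Protocol article*

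**What the plan says.** Under Intervention delivery the article states: "Participants will be permitted to continue to see any outside mental health professionals during the trial". The next sentence is the commitment at issue: "In these instances, outside interventions will be documented and controlled for during data analysis". Eligibility likewise leaves usual care open: "Participation will not require alteration to usual care including use of any medication or psychotherapy".

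Under Data analysis the article commits to intention to treat ("We will perform analysis according to the intention-to-treat principle") and explains this to mean that "participants will be analyzed according to the treatment group to which they will be randomly allocated regardless of dropout or treatment adherence status". The comparison is a baseline-adjusted repeated-measures ANCOVA, with mixed-effects models for scores over time. The candidate covariates are given as: "Time since diagnosis, education, marital status, medical comorbidities, and age will be examined as potential covariates to model". Outside care is not among them.

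Under Demographic and clinical information, "past/current psychosocial service use" is collected together with the demographic items. Table 2 marks Demographics at T0 only.

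Hypotheses makes change in depressive and anxiety symptoms to 12 weeks post intervention a primary outcome of consideration. It adds that the distress results will feed sample size estimates for later trials.

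**The concern.** Outside care used during the trial is recorded after randomisation. A man who still feels distressed is more likely to keep up or step up outside therapy, and one who feels better may drop it. GET is designed to lower distress, and its fifth session covers self-care behaviour, so outside use could plausibly differ by arm.

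If it does, putting it in the model has two effects:

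- It removes whatever part of the arm difference runs through outside care.
- Because use and outcome share unmeasured causes, such as severity not captured by the baseline score, it links arm to those causes within levels of use.

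Randomisation protects a contrast adjusted for pre-randomisation variables. It does not protect one adjusted for a possible consequence of treatment.

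What is at stake is the distress estimate that the pilot passes on to the design of a larger trial. There is also a plain mismatch to resolve: one section says the variable will be controlled for, and the section that lists the covariates omits it.

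**Working it through.** **No figure to reproduce.** The sample of 60, randomised 1:1, is justified under Study design by recruitment estimates and minimal analysis requirements. No effect size, SD, power or rate of outside care is given. The question is whether the stated adjustment can shift the contrast, so it was checked by large-sample simulation (400,000 men per scenario). Every input below is an assumption.

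**Model.** Let g be the arm (1 = GET), u an unmeasured distress factor, b the baseline score and T on-trial outside care.

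- b = 0.5u + 0.6 × noise
- logit P(T = 1) = logit(0.30) + c·u + s·g, with c = 0 or 1 and s = 0, -0.7 or -1.4
- outcome = 0.5b + 0.5u - 0.40g + β·T + 0.7 × noise, with β = 0, -0.3 or -0.6

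Three regressions were fitted: arm and baseline score (intention to treat); the same plus on-trial use; the same plus outside-care status at baseline.

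| Scenario | Use GET / ISP | β | Shared factor (c) | Intention to treat | Adjusted for on-trial use | Shift |
|---|---|---|---|---|---|---|
| A | 33% / 33% | -0.6 | 1 | -0.401 | -0.401 | 0.000 |
| B | 17% / 30% | 0 | 0 | -0.400 | -0.400 | 0.000 |
| C | 9% / 30% | -0.6 | 0 | -0.273 | -0.397 | -0.124 |
| D | 13% / 33% | 0 | 1 | -0.402 | -0.348 | +0.054 |
| E | 13% / 33% | -0.3 | 1 | -0.338 | -0.345 | -0.007 |
| F | 13% / 33% | -0.6 | 1 | -0.277 | -0.344 | -0.068 |

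(Shifts come from unrounded estimates.)

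**Reading the table.**

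- A: arm does not change use, so there is no bias, even though outside care works and shares a cause with the outcome.
- B: use differs by arm, but outside care is inert and shares no cause with the outcome, so again there is no bias.
- C: outside care works and GET lowers its use. By hand, total effect = -0.40 + (-0.6) × (0.09 - 0.30) = -0.40 + 0.126 = -0.274, matching the simulated -0.273. The adjusted model returns only the direct part and overstates the total effect.
- D: outside care is inert but shares a cause with the outcome. The adjusted model understates the effect.
- E and F: both mechanisms act and partly cancel.

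Adjusting for baseline status instead returned the intention-to-treat estimate in every scenario, to within 0.001.

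**Size against sampling error.** Before any contribution from T, the within-arm outcome variance is 0.25 × 0.61 + 0.25 + 2 × 0.25 × 0.5 + 0.49 = 1.1425, so the SD is about 1.07. The extreme shifts are then 0.124 / 1.07 = 0.12 SD and 0.054 / 1.07 = 0.05 SD. With 30 per arm the standard error in SD units is √(2/30) × √(1 - r²). This is 0.26 at an assumed baseline–outcome correlation of 0, and 0.18 at 0.7. The largest shift is therefore 0.12 / 0.26 = 0.46 to 0.12 / 0.18 = 0.67 of a standard error.

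**Carry-over to a later sample size.** Required n varies as 1/effect². With the SD held fixed, using the adjusted estimate in C would multiply n by (0.273 / 0.397)² = 0.47. In D it would multiply n by (0.402 / 0.348)² = 1.33. These are the ends of an assumed range, not predictions.

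**The case against.** The best reply is that the article means entry status. It speaks of men who continue to see someone, which describes care already under way. The only service-use measure it names sits with the demographics, scheduled at T0. Adjusting for that would be harmless, and the analysis section contains no model with on-trial care in it. This reading is plausible, but the article does not state it. The sentence refers to care during the trial, says it will be documented, and sets no restriction. Even for care already under way, continuing, stopping or intensifying it happens after allocation.

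A second reply is that intention to treat, as the article defines it, concerns the group in which each man is analysed, and a covariate moves nobody. That is right. A reader might infer that the two sections flatly contradict each other on intention to treat, and the text does not support that. What can change is the quantity estimated: it may no longer be the total effect of allocation.

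Third, ISP is an active six-session comparator, so a difference in outside use is not a given. This stands, and it is why the point is conditional.

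Fourth, this is an external pilot. The Discussion treats observed change as preliminary and bases its main conclusions on whether and how to proceed. That lowers the weight of the point. It does not remove it, because the distress results are to inform later sample sizes.

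**Conclusion.** The concern holds in conditional form. As written, the plan controls for outside care used during the trial without limiting this to pre-randomisation care, and the covariate list does not match. If arm affects that use, the adjusted distress contrast could depart from the intention-to-treat effect in either direction. If use is unaffected by arm, there is no such bias.

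Three stronger readings go too far:

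- That the contrast is biased as a matter of fact. The article gives no rate of outside care and no evidence that it would differ by arm.
- That the direction follows from whether GET lowers or raises help-seeking. With GET lowering use, the effect was overstated in C and understated in D.
- That the sign could reverse. No scenario examined showed this.

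The size cannot be derived from the document. Under the assumed inputs the shift ran from -0.124 to +0.054 on a scale with an SD of about 1.07, at most about two-thirds of a standard error with 30 per arm. Given that and the pilot purpose, this is a should-fix.

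**What to change.** Revise the sentence under Intervention delivery along these lines: outside mental health care during the trial will be documented and reported by arm; it will not be a covariate in the main intention-to-treat comparison; psychosocial service use at T0 may be a covariate; on-trial care will enter only an analysis labelled as a sensitivity analysis.

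Align Data analysis with this by adding T0 service use to the candidate covariates, if it is wanted, and by naming the sensitivity analysis. If entry status was meant all along, the same wording says so.

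The cost is a sentence in each of the two sections. No new data appear to be needed, because past and current service use is already collected with the demographics, which Table 2 places at T0, and the article already undertakes to document on-trial care. The change does not touch what care participants may receive.
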